### Statistical analysis

A detailed statistical analysis plan (SAP) will be developed during the delivery phase of the trial, agreed with an independent statistician, and made publicly available via the VeRMiS website, prior to final database lock.

The primary analysis of the primary outcome will be undertaken in line with a modified Intention-to-Treat (ITT) principle amongst participants with complete data at baseline and 26 weeks. The primary analysis will utilise analysis of covariance (ANCOVA), with robust standard errors if necessary, comparing DHI at 26 weeks between the two allocated groups, adjusted for baseline DHI scores, as well as the minimisation factors described previously. Between-group mean differences will be presented with 95% confidence intervals wherever possible, and hypothesis testing will be undertaken at the 5% significance level.

Sensitivity analyses of the primary outcome will be undertaken, possibly including but not limited to per protocol or complier-average causal effect (CACE) analyses. A CACE analysis can provide an unbiased estimate of the intervention effect based on those who complied with their allocated group’s protocol. Additional adjustments in the ANCOVA model will be considered, if any notable imbalances between groups at baseline are observed, in order to investigate the robustness of the conclusions of the primary analyses.

Secondary outcomes will also be analysed using ANCOVA and exploring variable transformations where appropriate.

#### Exploratory and subgroup analyses

Exploratory analyses will be considered which will help to inform future studies. These include:
Exploration of the impact of the following covariates on changes with treatment:
diagnosis (central versus peripheral versus combined vestibulopathy)visual dependency as determined by the rod and disc testpsychological state as determined by the HADSassociated symptoms (knee extensor strength, reaction time, leg sensation, neck range of motion)Estimating the diagnostic accuracy of the bedside tests for vestibulopathy

The sensitivity and specificity of diagnosing central and peripheral vestibular disorders using the bedside tests for vestibulopathy compared to laboratory-based measures will be calculated and presented with 95% confidence intervals for the estimates. This is an exploratory analysis that will inform future studies. The relationship between the diagnosis according to clinical tests and recovery with rehabilitation will be explored using an additional subgroup analysis.

### Economic evaluation

The economic evaluation will establish the resources required to provide the customised and booklet based VR, estimate the cost of the interventions, and conduct a full cost-effectiveness analysis (CEA). The intervention costing and CEA, based on within-trial data collection, will be undertaken from the primary perspective of NHS/Social Care. Participant and broader societal perspectives will be considered in sensitivity analyses. The CEA will synthesise cost and outcome data to present incremental cost-effectiveness ratios (ICERs) i.e. the incremental cost per unit of additional outcome. The CEA will present an ICER for the primary outcome (Dizziness Handicap Inventory) and the primary economic endpoint of policy relevance (the QALY). Cost-effectiveness acceptability curves will be presented, as appropriate.

Intervention resource requirements (e.g. physiotherapist time, travel, telephone calls, documentation etc.) and costs will be estimated by case report forms. Self-reported health and social care resource use data will be collected at baseline, 14 weeks (+/− 2 weeks) and 26 weeks (+/− 2 weeks) [90]. This will include primary, secondary and social care, and participant and carer-related resource use data. The EQ-5D-5L will be used to estimate QALYs for use as the primary economic endpoint. Incremental costs and incremental QALYs over 3 months will be used to estimate the cost-per-QALY for customised VR versus the generic booklet-based exercise. A sensitivity analysis will also explore the cost-effectiveness of the intervention when the MSIS-8D or MSIS-8D-P is used as a condition-specific QALY alternative to the EQ-5D. Descriptive statistics will summarise the costs (by type of service) and QALYs. A regression model will be used to adjust for systematic differences between intervention and control arms that have not been accounted for by randomisation. If appropriate, multiple imputation will be used to correct for bias that may result from data that is missing at random, e.g. EQ-5D-5L or cost data [91]. Analyses will also explore uncertainty, and provide a clear, policy-relevant presentation of findings.

### Nested observational study

Treatment plan: Following the diagnosis of BPPV at the initial screening assessment an Epley or Semont manoeuvre will be performed for people identified as having a posterior canal BPPV [57]. The type of manoeuvre chosen will be recorded and determined by factors such as the ability of the participant to move and range of motion and pain in the neck. Participants diagnosed with horizontal canal BPPV will have treatment with the “barbecue rotation” manoeuvre [92] or Forced Prolonged Position [93]. After the manoeuvre BPPV will be re-tested. Up to two manoeuvres will be performed.

Participants will be asked to return to the clinic after 1 week to re-test for any residual BPPV (session 2. The appropriate test for BPPV will be repeated. If the test for BPPV is negative (the primary outcome measure) and participants are symptom free (based on a Vertigo Symptom Scale score < 0.3/4) they will be re-tested on the secondary outcome measures (questionnaires and Dynamic Gait Index DGI). If the test for BPPV is positive the appropriate manoeuvre will be repeated (Eply/Semont or barbecue rotation). After the manoeuvre BPPV will be re-tested. Up to two manoeuvres will be performed.

Participants who still have a positive diagnosis of BPPV in session 2 will be asked to return again to clinic 1 week later. People will be tested for BPPV (the primary outcome measure) and the secondary outcome measures (questionnaires and DGI). If the test for BPPV is negative (the primary outcome measure) and participants are symptom free (based on a Vertigo Symptom Scale score < 0.3/4) no further action will be taken. If the test for BPPV is positive or if people have ongoing vertigo and/or balance and gait impairment they will be provided with a self-management “Balance rehabilitation” booklet providing comprehensive advice on VR exercises. The number of treatment sessions and manoeuvres performed will be recorded.

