# Vestibular rehabilitation in multiple sclerosis: study protocol for a randomised controlled trial and cost-effectiveness analysis comparing customised with booklet based vestibular rehabilitation for vestibulopathy and a 12 month observational cohort study of the symptom reduction and recurrence rate following treatment for benign paroxysmal positional vertigo

**DOI:** 10.1186/s12883-020-01983-y

**Published:** 2020-11-27

**Keywords:** Multiple sclerosis, Vestibular, Vertigo, Balance, Benign paroxysmal positional vertigo, Vestibulopathy, Rehabilitation, Randomised controlled trial

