**Methods/ design:**

People with MS and symptoms of vertigo, dizziness and/or imbalance will be screened for central and/or peripheral vestibulopathy and/or BPPV. Following consent, people with BPPV will be treated with re-positioning manoeuvres over 1–3 sessions and followed up at 6 and 12 months to assess for any re-occurrence of BPPV. People with central and/or peripheral vestibulopathy will be entered into a randomised controlled trial (RCT). Trial participants will be randomly allocated (1:1) to either a 12-week generic booklet-based home programme with telephone support or a 12-week VR programme consisting of customised treatment including 12 face-to-face sessions and a home exercise programme. Customised or booklet-based interventions will start 2 weeks after randomisation and all trial participants will be followed up 14 and 26 weeks from randomisation. The primary clinical outcome is the Dizziness Handicap Inventory at 26 weeks and the primary economic endpoint is quality-adjusted life-years. A range of secondary outcomes associated with vestibular function will be used.

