## Participants

### Eligibility criteria

#### Inclusion criteria

The study population will comprise individuals diagnosed with MS (relapsing remitting, primary or secondary progressive) according to McDonald’s revised criteria [55, 56]. These participants will:
be aged > 18 yearsbe willing and able to consentscore 1–6 on Patient Determined Disease Steps, equivalent to Expanded Disability Status Scale (EDSS) 2–6.5report one of the following at least 4 times/month:
◦ feeling that things are spinning or moving around◦ a feeling of being light-headed, “swimmy” or giddy◦ feeling unsteady and about to lose balancewilling and able to travel to, and participate in, the 12 face to face sessions should they be allocated to the intervention group and to commit to undertaking their individualised home-based programmewilling and able to travel to local assessment centres for screening and baseline tests and blinded outcomes assessment.People eligible for the nested observational study will in addition have a a positive diagnosis of BPPV determined by tests for posterior (Dix- Hallpike) and horizontal canal BPPV (horizontal head rotation in supine with the head in 30^o^ flexion) [57].

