#### Screening for BPPV

Participants will be screened for posterior canal BPPV using the Dix-Hallpike manoeuvre and horizontal canal BPPV using a roll test. Those with a positive BPPV test will be excluded from the RCT and treated with the appropriate re-positioning manoeuvre. After providing informed consent, these individuals will then be entered into an observational study and followed up at 6 and 12 months to assess for any re-occurrence of BPPV, as detailed in the section “Nested observational study”.

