#### Data measurement

Primary and secondary outcomes will be tested at the end of the treatment session (session 2 or 3) and at 26 and 52 weeks (+/− 2 weeks) after their last treatment appointment.

The primary outcome measure is the clinical test for BPPV (Dix- Hallpike) and (horizontal head rotation with the head in 20^o^ flexion).

Secondary outcome measures will be subjective vestibular specific questionnaires (Dizziness Handicap Inventory [68], MS-12 item self-report walking scale Version 2.0 [81]; Activities-Specific Balance Confidence Scale [82]; Vertigo Symptom Scale- Short Form [59, 83]; Situational Characteristic Questionnaire [52]; Fatigue Scale for Motor and Cognitive functions (FSMC) [84]; Hospital Anxiety and Depression Scale (HADS) [85]; 29-item Multiple Sclerosis Impact Scale [MSIS-29] Version 2.0 [86, 87]) and the Dynamic Gait Index [68, 94].

Participants will be asked to record re-occurrence of their symptoms on a re-occurrence/ AE form during this time if they experience vertigo again so the time of re-occurrence can be noted. If symptoms reoccur participants will be referred to their GP.

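### At session 2 the BPPV cohort's Treatment plan ties secondary-outcome measurement to being symptom free, in conflict with Data measurement and leaving test-negative, still-symptomatic participants without an end-of-treatment measurement

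*Protocol article*

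**What the plan says.** All references are to the protocol article.

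**Nested observational study, Treatment plan.** At session 2, one week after the first manoeuvre, the positional test is repeated in everyone. What follows depends on the result:

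- Test negative: "and participants are symptom free (based on a Vertigo Symptom Scale score < 0.3/4) they will be re-tested on the secondary outcome measures". Two conditions are joined: a negative test and a low VSS score.
- Test positive: "If the test for BPPV is positive the appropriate manoeuvre will be repeated", and the participant is asked back a week later.
- At session 3, everyone who attends has the positional test, the questionnaires and the DGI. The symptom criterion is applied afterwards, only to decide on further action.

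**Nested observational study, Data measurement.** "Primary and secondary outcomes will be tested at the end of the treatment session (session 2 or 3"), and again at 26 and 52 weeks. No symptom condition is attached. The short form of the VSS is itself on the list of secondary outcomes.

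**Title.** The cohort is described as a "12 month observational cohort study of the symptom reduction and recurrence rate following treatment for benign paroxysmal positional vertigo". The Analysis section puts the primary interest on the recurrence rate.

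**Horizontal-canal test.** Under Inclusion criteria it is "horizontal head rotation in supine with the head in 30^o^ flexion". Under Data measurement, as part of the primary outcome, it is "horizontal head rotation with the head in 20^o^ flexion".

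**The concern.** Session 2 has three possible kinds of participant, and the Treatment plan provides for two. The third, test negative but with a VSS score of 0.3 or more, is neither measured on the secondary outcomes nor recalled. This group is foreseeable. Entry symptoms include unsteadiness and light-headedness, the Background attributes balance impairment in MS to weakness, sensory loss, ataxia and spasticity as well, and the Treatment plan itself expects ongoing vertigo or balance impairment at session 3. The documents give no figure for how common it is.

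The condition for being measured is a score on a secondary outcome, so the missing data would not be missing at random: those left out are by definition the more symptomatic of the test-negative participants. At stake is the end-of-treatment symptom change, a secondary result, but one that the title announces. These participants also say most about whether clearing BPPV is enough to relieve symptoms in people with MS.

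The differing head positions are a separate and smaller matter. As written, the test that admits a participant is not the test that later decides success or recurrence.

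**Working it through.** **1. The plan's own figures.** The plan gives no number for symptom change. The cohort's only sizing figures are the margins of error in Table 1, and they concern recurrence. With x = round(n × p), the half-width of the Clopper-Pearson 95% interval at n = 63 (70 × 0.9) is 8.0, 9.3, 10.6, 11.3, 11.9 and 12.3 for 10% to 35%, exactly as printed. The point does not touch this table.

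**2. The two sections side by side (end-of-treatment secondary outcomes).**

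| Session 2 status | Treatment plan | Data measurement |
|---|---|---|
| Negative, VSS < 0.3 | measured at session 2 | measured at session 2 or 3 |
| Negative, VSS ≥ 0.3 | no measurement, no recall stated | measured at session 2 or 3 |
| Positive | recalled; all attenders measured at session 3 | measured at session 2 or 3 |

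The conflict lies in the middle row.

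**3. How many could be left out.** Let p be the share test negative at session 2 and s the share of those who are symptom free. The unmeasured share is p(1 − s). The documents give neither, so both are assumed:

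- p = 0.5, s = 0.9: 0.5 × 0.1 = 5%, about 4 of the anticipated 70.
- p = 0.7, s = 0.7: 0.7 × 0.3 = 21%, about 15 of 70.
- p = 0.9, s = 0.3: 0.9 × 0.7 = 63%, about 44 of 70.

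Under Data measurement the share is 0.

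**4. Size of the overstatement, main assumed case.** The VSS scale (0 to 4) stands in for a symptom outcome. Assume a baseline mean of 1.2 and a true post-treatment mean of 0.8 (SD 0.6, gamma distributed), the same for participants who reach session 3. The true reduction is 1.2 − 0.8 = 0.40. For this gamma distribution, 0.196 lie below 0.3, with mean 0.179.

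Observed mean = [p × 0.196 × 0.179 + (1 − p) × 0.8] / [p × 0.196 + (1 − p)]

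- p = 0.5: (0.0175 + 0.400) / 0.598 = 0.698. Apparent reduction 0.50; ratio 1.25.
- p = 0.7: (0.0246 + 0.240) / 0.437 = 0.606. Apparent reduction 0.59; ratio 1.49.
- p = 0.9: (0.0316 + 0.080) / 0.276 = 0.404. Apparent reduction 0.80; ratio 1.99.

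**5. A second set of assumptions.** Baseline mean 1.5, mean 0.15 if symptom free and 1.0 if symptomatic, p = s = 0.7:

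- All measured: 1.5 − (0.7 × 0.15 + 0.3 × 1.0) = 1.5 − 0.405, about 1.09.
- Treatment plan followed literally: observed mean = (0.49 × 0.15 + 0.30 × 0.405) / 0.79 = 0.247, reduction 1.25, which is about 15% too large.

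**6. Carrying this over to the outcomes actually missing.** VSS must be scored to apply the condition, so the data lost are DHI, DGI and the other questionnaires. In step 4 the excess reduction is 0.10 to 0.19, or 0.17 to 0.32 SD (dividing by 0.6), for p = 0.5 to 0.7. For an outcome linearly related to VSS with correlation r, the excess is r times that. At r = 0.5 and the same standardised true change, the ratios 1.25 and 1.49 become 1.13 and 1.24.

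**The case against.** The strongest reply is that Data measurement is the section that governs outcome timing, and it has no symptom condition. The Treatment plan describes care, does not say that only symptom-free participants are measured, and does not say that the others go unmeasured. On that reading nothing is selected. This stands as a possible reading and is why the point is a conflict and not a demonstrated bias. It does not remove the problem, because the article does not say which section prevails and the Treatment plan is the step-by-step instruction for session 2.

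Several stronger readings are tempting, and the documents do not support them.

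- **That post-treatment VSS exists only for people with low VSS.** The score has to be taken in all test-negative participants to apply the rule.
- **That the overstatement is the gap among session 2 finishers alone** (1.2 − 0.18 = 1.02 against 0.40 in step 4). No analysis is restricted to that subgroup, session 3 attenders are measured whatever their symptoms, and VSS is the one outcome that need not be missing.
- **That the cohort's main results are biased.** The positional test is repeated at session 2 without a symptom condition, the stated primary interest is recurrence, and the 26- and 52-week visits are not gated. The Analysis section defines no symptom-change estimator.
- **That consent is placed inconsistently.** The abstract has "Following consent, people with BPPV will be treated with re-positioning manoeuvres", whereas Screening for BPPV mentions treatment first and then "After providing informed consent, these individuals will then be entered into an observational study". The latter can be read as consent to cohort entry, with the manoeuvre given as care; this is loose wording and has no bearing on outcome selection.
- **That there is no pre-treatment measurement.** The Treatment plan's word for session 2 is re-tested, which implies an earlier measurement, and a condensed article may leave the schedule to the full protocol.

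**Conclusion.** The point holds as a conflict between two sections with a possible consequence for one secondary result. Read literally, the Treatment plan gives test-negative, still-symptomatic participants no end-of-treatment DHI, DGI or other questionnaire, and Data measurement requires one. If the Treatment plan is what sites follow, the end-of-treatment change in those measures is selected on symptom status and too favourable.

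The documents contain no figure from which the size can be fixed. The range of about 1.25 to 1.5 times rests on an assumed VSS distribution, on 50-70% being test negative at session 2, on session 3 attenders having the same true mean, and on the missing outcome tracking VSS closely; with a weaker correlation it is smaller. If Data measurement governs, the bias is nil.

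The 30 versus 20 degree difference in the horizontal-canal test is a genuine inconsistency in a component of the primary outcome. No size can be put on it from the documents.

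**What to change.** 1. Reconcile the Treatment plan with Data measurement so that the secondary outcomes are recorded at session 2 in every test-negative participant whatever the VSS score. Report symptom-free status (VSS below 0.3) as a result, and do not use it as a condition for measurement. Session 3 already works this way.
2. State the pathway of test-negative, still-symptomatic participants after session 2, so that the sections agree. Which pathway is a clinical matter for the investigators; no rule is proposed here.
3. Reconcile the head position for the horizontal-canal test between Inclusion criteria and Data measurement, so that entry and outcome rest on the same test. Which angle is right is likewise left to the investigators.
4. If participants have already passed session 2 under the literal rule, report how many test-negative participants lack the end-of-treatment questionnaires, with their session 2 VSS scores.

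The cost is a change of wording and one set of questionnaires and DGI for people already in the clinic. Sample size and the recurrence analysis are unchanged.

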#### Data measurement

Primary and secondary outcomes will be tested at the end of the treatment session (session 2 or 3) and at 26 and 52 weeks (+/− 2 weeks) after their last treatment appointment.

The primary outcome measure is the clinical test for BPPV (Dix- Hallpike) and (horizontal head rotation with the head in 20^o^ flexion).

Secondary outcome measures will be subjective vestibular specific questionnaires (Dizziness Handicap Inventory [68], MS-12 item self-report walking scale Version 2.0 [81]; Activities-Specific Balance Confidence Scale [82]; Vertigo Symptom Scale- Short Form [59, 83]; Situational Characteristic Questionnaire [52]; Fatigue Scale for Motor and Cognitive functions (FSMC) [84]; Hospital Anxiety and Depression Scale (HADS) [85]; 29-item Multiple Sclerosis Impact Scale [MSIS-29] Version 2.0 [86, 87]) and the Dynamic Gait Index [68, 94].

Participants will be asked to record re-occurrence of their symptoms on a re-occurrence/ AE form during this time if they experience vertigo again so the time of re-occurrence can be noted. If symptoms reoccur participants will be referred to their GP.

#### Analysis

The analyses for observational study will take cognisance of the STROBE guidance [95]. The primary interest in the observational study is on the BPPV reoccurrence rate. The success rate following treatment for BPPV will be estimated and presented with 95% confidence intervals.

The short term (1 week) and longer term (6 and 12 months) reoccurrence rates in people with MS will be estimated and presented with 95% confidence intervals. These rates will be compared to standardised effect sizes from previous literature monitoring BPPV treatment outcomes in people with BPPV and without any additional pathology.

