In BPPV, otoconia crystals become dislodged from the otolith macula and become trapped within the semicircular canals; usually the posterior canal is affected. BPPV can be diagnosed using the Dix-Hallpike manoeuvre that moves the head in the plane of the posterior canal. When otoconia are present in the canal this leads to deviation or deflection of the cuplua and reflexive, characteristic eye movements. BPPV is treatable with bedside physical manoeuvres such as Epley or Semont, which aim to move these crystals back into the otoliths. A Cochrane systematic review highlights that compared to no intervention these manoeuvres, in otherwise healthy participants, are very effective at reducing symptoms of vertigo (odds ratio 4.42[2.62–7.44]) and producing a negative Dix –Hallpike test (odds ratio 9.62 [6–15.42]) [24]. However, symptoms can re-occur in 36% of cases over 48 months [24] and re-occurrence rates are greater in people with migraine or head injury [25, 26]. It is unclear whether repositioning manoeuvres have the same short and long term effectiveness in people with MS compared to the general, otherwise healthy, population. Currently, testing and repositioning manoeuvres for BPPV in people with MS are not routinely performed. Therefore, nested within this study, we plan to undertake a observational study to determine the success rate of repositioning manoeuvres and re-occurrence rate of symptoms in pwMS who are assessed as having BPPV.

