#### Observational study

Based on being able to recruit 140 participants to the main project (given the resources available), and assuming approximately 50% of pwMS present with BPPV [22, 23], it is anticipated that approximately 70 people will be enrolled in the observational study. The primary aim of the observational study is to estimate the recurrence rate of BPPV. Based on data from Hilton et al. 2014 [24], the expected precision of the estimate of recurrence, based on a range of sample sizes and recurrence rates, and after allowing for 10% loss to follow-up by the end of the one-year period, are provided in Table 1.

**Table 1 Tab1:** Expected precision of the estimate of recurrence, based on a range of sample sizes and recurrence rates, after allowing for 10% loss to follow-up by the end of the one- year period. These are based on exact confidence intervals for the proportion of recurrences, using the Clopper-Pearson method

Sample size		Estimated margin of error (%)					
Total number of participants recruited to trial 2	Total number of trial 2 participants followed-up	Recurrence rate (%)					
		10	15	20	25	30	35
30	27	13.4	14.8	15.9	17.6	18.2	18.7
35	32	11.5	13.8	14.6	16.0	16.5	17.3
40	36	11.5	12.4	13.9	15.0	15.9	16.5
45	41	10.2	11.8	13.0	14.0	14.7	15.3
50	45	10.2	11.5	12.5	13.3	14.2	14.7
55	50	9.2	10.5	11.8	12.6	13.4	13.8
60	54	8.6	10.3	11.4	12.3	12.8	13.3
65	59	8.5	9.9	10.9	11.7	12.3	12.7
70	63	8.0	9.3	10.6	11.3	11.9	12.3
75	68	7.9	9.1	10.2	10.8	11.4	11.9
80	72	7.5	8.9	9.7	10.5	11.1	11.5

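### BPPV recurrence proportions are to be compared with standardised effect sizes at no matched follow-up time, and would miss episodes between visits if only the 26- and 52-week tests count

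*Protocol article*

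**What the plan says.** The sample size section for the cohort sets the target: "The primary aim of the observational study is to estimate the recurrence rate of BPPV". It plans precision for a simple proportion at one year. Under Nested observational study, Data measurement, the primary outcome measure is the clinical positional test, and the schedule is: "Primary and secondary outcomes will be tested at the end of the treatment session (session 2 or 3) and at 26 and 52 weeks" (plus or minus 2 weeks) after the last treatment appointment. Between visits, participants note any return of vertigo on a re-occurrence/adverse event form so that its time is known, and "If symptoms reoccur participants will be referred to their GP". No study positional test at that moment is described.

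The Analysis section makes the recurrence rate the primary interest, at 1 week, 6 and 12 months with 95% confidence intervals. It does not say whether a recurrence is a positive test, a form report, or either. It ends with the comparison: "These rates will be compared to standardised effect sizes from previous literature monitoring BPPV treatment outcomes", in people with BPPV and no additional pathology. The one recurrence figure in the protocol is in the Background: "symptoms can re-occur in 36% of cases over 48 months".

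**The concern.** There are two separate problems.

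The first is the comparator. A recurrence rate in a single cohort is a proportion. A standardised effect size is a difference between means in standard deviation units, and the protocol uses the term that way in the trial's own sample size section (1.03 and 1.12 for change in DHI). The BPPV figures it cites from the literature are odds ratios and one recurrence proportion; none is a standardised effect size. The follow-up time of the published rate is also left open, although the cited proportion runs four times as long as the cohort.

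The second is the event. A test at two fixed visits measures who is positive on those days. A participant whose BPPV returns in month 3 and has resolved or been treated by week 26 can test negative at both visits. Published recurrence is usually wanted as a cumulative quantity. If a two-visit prevalence were set beside a cumulative figure over a longer period, recurrence in MS could look no higher than in otherwise healthy people for reasons of measurement alone.

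**Working it through.** **1. The plan's own precision figures.** The inputs are the expected enrolment ("it is anticipated that approximately 70 people will be enrolled in the observational study"), the 10% loss by one year, which leaves 63, and the Clopper-Pearson method named under Table 1. With n = 63 and whole-number counts x = 6, 9, 13, 16, 19, 22 (10% to 35%), the half-widths of the exact 95% interval are 8.0, 9.3, 10.6, 11.3, 11.9 and 12.3 points. These equal the printed row. For example, x = 13 gives 11.5% to 32.7%, and (32.7 − 11.5)/2 = 10.6. The table is sound, but it covers sampling error only.

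**2. The cited figure at the cohort's follow-up time.** The input is 36% at 48 months (Background). How recurrences spread over time is an assumption.
- Constant hazard: h = −ln(0.64)/48 = 0.0093 per month. F(12) = 1 − 0.64^(12/48) = 10.6% and F(6) = 1 − 0.64^(6/48) = 5.4%.
- Linear: 36% × 12/48 = 9.0% at 12 months.

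If the 36% were used unadjusted against a 12-month rate, the mismatch would be 36/10.6 = 3.4-fold (constant hazard) or 36/9.0 = 4-fold (linear).

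**3. What two visits would find if only tests counted.** Suppose an episode stays test-positive for d months (assumed; the protocol gives no duration), and take the visits as 6 and 12 months. The captured share of participants is [F(6) − F(6 − d)] + [F(12) − F(12 − d)], with F(t) = 1 − exp(−ht).

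| d (months) | Captured | True F(12) | Share found |
|---|---|---|---|
| 1 | 1.7% | 10.6% | 16% |
| 2 | 3.5% | 10.6% | 33% |
| 3 | 5.2% | 10.6% | 49% |

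In 63 participants the true count would be 63 × 0.106 = 6.7. The calculation gives no credit for a second episode that happens to be present at a visit, so it leans towards a larger loss.

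**4. The same loss without a duration assumption.** If a share f of true recurrences is missed, the expected estimate is R(1 − f). At R = 20%, f = 0.25 gives 15.0% and f = 0.50 gives 10.0%. The second shift, 10 points, is about the size of the 10.6-point sampling margin in Table 1. If form reports are counted, f shrinks to the share neither reported nor test-positive.

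**The case against.** A reader might infer that recurrence is undercounted as a matter of fact. The text does not support that. The Analysis section does not exclude the re-occurrence forms, dating the events would serve little purpose if only visit tests mattered, and several statements of aim speak of recurrence of symptoms, which is what the form records. If unconfirmed form reports count, the bias may run upward, because vertigo in MS has other causes. This stands: the undercount is conditional on a test-only reading.

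A reader might also infer that there is no valid comparator. That too is more than the protocol shows. A reference population is named and a recurrence proportion is cited. The Analysis section refers to earlier literature in general and does not tie the comparison to the 48-month figure. The planning range of 10% to 35% at one year contains the 10.6% derived above, so the plan does not presume 36% at 12 months. The mismatch is what would follow from using that figure directly, not something the plan commits to.

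Finally, event definitions and the choice between a simple proportion and a time-to-event estimate are often left to the analysis plan, which is promised but not shown. Silence on those points alone would be no finding. What does not fall under this defence is the comparison with standardised effect sizes, which is stated and wrong, and the naming of the visit test as the primary measure for a rate whose between-visit events are recorded elsewhere.

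**Conclusion.** The point holds in two parts of different strength. The comparator metric is wrong on the face of the text, whatever one assumes, and the follow-up time of the comparison needs to be fixed. The cited 36% corresponds to roughly 9% to 11% at 12 months only under a linear or constant-hazard course.

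The risk of missed recurrences is real but conditional. It arises if only the scheduled tests count, and its size cannot be set from the protocol. The range of 16% to 49% of first recurrences found rests on test-only counting, a constant hazard, episodes that stay positive for 1 to 3 months, and no credit for repeat episodes. It is a scenario, not an estimate of bias in this study. The matter concerns the cohort's primary interest and leaves the randomised comparison untouched.

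**What to change.** In the Analysis section, replace the reference to standardised effect sizes with published recurrence proportions or rates at the same follow-up time, 6 and 12 months.

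Among participants with a negative end-of-treatment test, so that only those who cleared are at risk of recurrence, report both:
- (a) recurrence by positive test at a visit, with its exact interval as planned;
- (b) cumulative incidence to 6 and 12 months, counting the first of a positive test or a dated re-occurrence-form event.

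Label (b) an upper bound, because vertigo in MS need not be BPPV. Show any GP-confirmed BPPV as supporting information and do not require it for an event: the Background says that BPPV testing in people with MS is not routine, so a definition that depended on GP confirmation could itself miss events.

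The cost is a change of wording in the protocol or analysis plan and a little more analysis, since the dated forms are already collected. The downside is a second estimate that may overcount. No change to clinical management is proposed.
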